**Fig. 1 Fig1:**
[figure not shown]
Study population & selection method in Austria

#### Czech Republic

The 159 nursing homes (see Fig. 2) of Central Bohemia and the Prague region (from a total of 822 nursing homes in the Czech Republic) formed the basis for the Czech randomized selection process (100 homes of the category “homes for seniors” and 59 homes of the category “homes with a special regime”). Using a similar method as the Austrian team, 12 randomly selected homes were drawn (6 homes for seniors and 6 homes with a special regime) covering each sub-category (municipal, for-profit and non-profit). In the category “homes for seniors”, 6 nursing homes (3 municipal, 1 for-profit and 1 non-profit) consented to participate. In the category “homes with a special regime” four nursing homes (2 municipal, 1 for-profit and 1 non-profit) consented to participate. The resulting sample is very diverse in size – the smallest home provides services for 8 residents, whereas the biggest home provides care for 260 residents. In total, 570 residents are included in the Czech sample.

**Fig. 2 Fig2:**
[figure not shown]
Study population & selection method in the Czech Republic

### Study protocol

The study protocol used in both study centres assesses four different domains: a) Resident, b) Care team, c) Relative and d) Environmental Factors. ﻿In Table 1, study instruments and data sources are listed.

**Table 1 Tab1:** Instruments of the study protocol

Measurement/Variable	Measurement instrument/Items
Resident	
Dementia stage	Global Deterioration Scale (GDS)
Cognition	Brief Cognitive Rating Scale (BCRS)
	Mini Mental Status Examination (MMSE)
	Clock-drawing Test
Functioning	Functional Assessment Staging Test (FAST)
	KATZ Index of Independence in Activities of Daily Living
Mobility	Timed Up and Go Test
Nutrition	Mini Nutritional Assessment (MNA, short form)
Pain	Visual Analog Scale for Pain (VAS)
	Pain Assessment in Advanced dementia (PAINAD)
Behaviour	Behavioural Pathology in Alzheimer’s disease Frequency Weighted Scale (BEHAVE-AD-FS)
	Empirical Behavioural Pathology in Alzheimer’s disease Rating Scale (E-BEHAVE-AD)
Quality of Life	Quality of Life in Alzheimer’s disease Scale (QOL-AD participant version)
Sociodemographic data	Age, sex, date of institutionalization, nationality
Medication	Type and dosage
Dental status	Prosthesis (yes/no), other
Number of falls in the last 6 months	Chart Review
Number of hospital stays	Chart Review
Needs Assessment	Focus groups and qualitative interviews^a^
Care Team	
Person-Centred Care	Person-Centred Care Assessment Tool (P-Cat)
Burden	Professional Care Team Burden Scale (PCTB)
Sociodemographic data	Age, sex, occupational group
Needs Assessment	Focus groups and qualitative interviews^a^
Relative	
Sociodemographic data	Age, sex, relationship link to resident
Number of Visits	Daily, Every 2 or 3 days, once per week/month, other
Quality of Life	Quality of Life in Alzheimer’s disease Scale (QOL-AD family version)
Needs Assessment	Focus groups and qualitative interviews^a^
Environmental Factors	
Organisational Category	A: Federal State, Municipality, Church & private CZ: Municipality, For-profit, non-profit
Size of Institution	Number of organizational units, employees, rooms and residents
Room facilities	various listed facilities
Social Activities	Number per month, duration per unit, number of participants
Care Concept	Name or description of the care concept

^a^Qualitative part of the study will be described in a separate publication

#### Residents

For the assessment of dementia severity, the Global Deterioration Scale (GDS) [33] is used. Within the GDS, each stage is numbered from 1 to 7. The stages 1 to 3 are pre-dementia stages and stages 4 to 7 constitute dementia stages. To assess cognition, the Brief Cognitive Rating Scale [34], the Mini Mental State Examination (MMSE) [35] and the Clock drawing-test [36, 37] are used. The Brief Cognitive Rating Scale (BCRS) was constructed in accordance with the Global Deterioration scale and distinguishes seven stages, ranging from normal cognitive capacity (stage 1) to very severe cognitive deficits (stage 7). The capacities are measured on five subscales (concentration, short-term memory, long term memory, orientation and functioning/self-care) [34]. The MMSE, a well-known “gold standard”, assesses orientation, attention, immediate and short-term recall, language and the ability to follow simple verbal and written commands. The Clock drawing test provides a visual record of cognitive ability in an easy and time saving fashion.

The Functional Assessment Staging Test (FAST) [36] and the Katz-Index of Independence in Activities of Daily Living (Katz-Index) [37] are used to assess daily functioning. The FAST scale consists of a hierarchical list of typical symptoms, covering seven main functional levels (1 through 7) [38]. In addition, symptoms occurring in a non- ordinal fashion can be scored indicating excess disability in a multi-morbid nursing home population. The Katz-Index rates daily performance in six areas (bathing, dressing, toileting, transferring, continence and feeding), ranging from 1 to 6, six describing full functional capacity, 4 moderate impairment and ≥ 2 severe functional impairment [39].

The Timed Up and Go Test is used to assess mobility [40]. Persons are instructed to rise from an arm chair, walk three meters, turn, walk back and sit down again. The longer the duration, the lower the capacity of a person to move around.

The short form of the Mini Nutritional Assessment (MNA) [41] is used to assess the nutritional status of the resident. Scores greater than 12 indicate an acceptable nutritional status, scores from 8–12 point to a risk of malnutrition and scores lower than 8 indicate a state of malnutrition.

The Visual Analog Scale for Pain (VAS Pain) [42] is used to assess pain intensity. Residents are asked to rate their pain on a scale, ranging from 0 (no pain) to 10 (severe pain). Additionally, the Pain Assessment in Advanced Dementia (PAINAD) scale [43] is used for persons who are unable to reliably communicate their pain due to dementia or cognitive impairment. The participants are observed for two to five minutes during activities like bathing, turning or transferring. There are five categories (breathing, negative vocalization, facial expression, body language, consolability), which can be rated from 0 to 2. The sum of these scores results in the total score ranging from 0 (no pain) to 10 (severe pain).

Behavioural symptoms are assessed using the Behavioural Pathology in Alzheimer’s Disease Frequency Weighted Severity Scale (BEHAVE-AD-FW) [44] and the Empirical Behavioural Pathology in Alzheimer’s Disease Rating Scale (E-BEHAVE-AD) [45]. Both behavioural scales consist of 25 symptoms grouped into seven categories, which are rated from 0 to 3. The BEHAVE-AD-FW is assessed within an interview with a care team member, while the E-BEHAVE-AD is a direct observational scale scored within the assessment of the resident.

In order to receive an impression about the Quality of Life of the residents, the Quality of Life in Alzheimer’s disease (QOL-AD) [46] and the Euroquol (EQ) 5D-3 L scale [47] are used. The QOL-AD measures Quality of Life through 13 items on a 4-point Likert scale, ranging from 1 (poor) to 4 (excellent). To assess the perspective of the residents, the QOL-AD (participant-version) is used. The family members also rate the Quality of Life of the resident via the QOL-AD (family version). The EQ-5D-3 L consists of two parts. In the first part, the health status of the resident is assessed with five questions. In each question the resident can choose between three possible answers, ranging from Level 1 (no problem) to Level 3 (extreme problems). In the second part, the resident has to assess the health status on a visual analogue scale, ranging from 0 to 100 [48]. All used scales are valid, reliable and well established instruments.

Further information on the resident are derived from the care record: sex, age, date of institutionalization, citizenship, dementia diagnosis, other medical diagnoses, medication, dental status, number of falls and hospital-stays in the last 6 months.

#### Care team

Since Kitwood’s concept of person-centred-care has become a quality criterion for dementia care, the Person-Centred Care Assessment Tool (P-CAT) [49] has been included. The P-CAT questionnaire aims at evaluating the degree to which the care team experiences their work as being person-centred. It consists of 13 items, each rated on a 5-point Likert scale, ranging from ‘disagree completely’ to ‘agree completely’. A satisfactory construct validity and a good reliability have been reported for the P-CAT [49]. The Professional Care Team Burden (PCTB) [50] scale is used to assess the burden of the care team members. This ten item scale assesses three domains of burden: structural, organizational and subjective burden. The PCTB has an acceptable internal consistency (Cronbach’s Alpha, 0.779) and was well received by the staff [50]. Additionally, information on sex, age, occupational category and duration of the employment at the institution in question are collected.

#### Relatives

Data on the relative’s demographic characteristics (sex and age) and the relationship link to the resident are collected, as well as the frequency of visits. The quality of life of the resident is rated from the relative’s perspective with the QUOL-AD (family version).

#### Environmental factors

The following variables on environmental factors are collected for each nursing home: the category and size of the nursing home, the number of organizational units (care units), the number of employees (full- and part-time), organizational structure (management, experience of management), supervision (yes/no, mandatory) and the number and equipment of rooms per floor. Furthermore, information on the care concept of the nursing home and on the available social activities (number of activities per month, duration of a unit in minutes and the average number of participants for each activity) are collected.

### Study protocol pilot testing

The scales used in this study are used in their authorized translation in the respective language (German and Czech). If there was no translation available (for example the PCTB did not exist in the Czech language), a forward-backward translation was performed by native speakers.

Feasibility of the protocol with respect to lengths and order of the instruments was tested in a small pilot study with some residents, care team members and relatives of non-participating nursing homes. After the testing phase, small adjustments were made.

### Study organization

Before the start of the data collection a workshop for all participating nursing home managers is organized in both countries. In this workshop the project is introduced and organizational issues are discussed. Additionally, an information workshop in each nursing home is held, inviting all care team members and relatives as well as residents. In order to promote an optimal study flow a time schedule is agreed upon and the necessity for a project assistant for each nursing home, chosen from the respective nursing home care team, is discussed. The project assistants are crucial for a smooth assessment process within each nursing home. First, they help the researchers (i.e. clinical psychologists) in daily matters, such as recruitment of the care staff and relatives for the assessments, and second, support the data collection process (for example in the chart review). These assistants are hired for the duration of the presence of the research staff in each particular nursing home. An attendance time for the research team of 1 month was calculated for each nursing home.

### Data management plan

The collection process itself is strictly controlled by a Data Management Plan (DMP).

The DMP consists of six major steps (see Fig. 3). In step 1, all basic requirements for the data management process were clarified. A key component is the database at the Danube University, where all quantitative project data will be stored in an anonymized fashion. This not only facilitates an easier monitoring of the data regarding quality, but also enables various analysis methods. To minimize the risk of data loss a multilevel backup is in place. On a weekly basis the contents of the server are saved on a tape drive, a dump of the database is stored in a secure cloud and in addition, the database manager creates monthly dumps on an external drive, which is locked at a special compartment at the data manager’s office. As the collected data are of sensitive nature, various security measures have been put in place. The connections to the database and its interface are restricted and controlled by the data manager. In addition, the IT-department of the University monitors any incoming and outgoing connections.

**Fig. 3 Fig3:**
[figure not shown]
Data management plan

Step 2 of the data management plan describes the user administration and security precautions, i.e. each database user has to sign a non-disclosure agreement. In order to guarantee data quality educational matters are described in Step 2 as well, thus in practice the data manager has to work closely with the field researchers. For example, they are instructed on how to correctly enter data into the frontend and on how to keep a research diary. This research diary is important to enhance the content of the meta-data. The actual data collection is coordinated in Step 3 of the data management plan. After the completion of the collection of quantitative data, the qualitative data collection is starting. These data are stored on the same server.

As step 4, a common quantitative data analysis is defined and the qualitative data are transcribed. In Step 5, the quantitative data are analysed, the qualitative data categorized and then the results will be summarized and synthesized for publications. Finally, the data will be made ready to share in Step 6 (funding for this process has been applied for).

### Statistical analysis plan and statistical considerations

The data will be exported from the database into CSV files via SQL-statements. Statistical analysis will then be performed via the open statistical software “R”. Descriptive statistics will be used to summarize the characteristics of the sample in the different countries and in the distinct nursing homes. A multilevel regression analysis will be performed per country to estimate the influence of different environmental and other factors (for example staffing) on the occurrence of neuropsychiatric symptoms. One particular issue will be the influence of the environments on the amount and severity of behavioural symptoms (e.g. the size of the nursing home, and patient/staff ratio). Another important issue will be the influence of the care team burden on the occurrence of behavioural problems. In addition, the correlation between the influence factors and the cognitive, functional und behaviour measurements will be investigated.

The distribution of the most important outcome variables and covariates will be used to check for outliers and differences between the two countries. Depending on the level of measurement Student’s *t*-test, Mann-Whitney *U* Test or *Chi*
^2^ Test will be used – especially for country comparison. Next, a pooled analysis will be performed and for the outcome variables, random effect models with the respective country as random factor will be conducted.

The statisticians of both project partners will cooperate on the definition of different topics of analysis.

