## Methods/Design

### Study design

DEMDATA is a multicentre mixed methods cross-sectional study. Stratified and randomly drawn nursing homes in Austria and the Czech Republic are surveyed. The project started in March 2016 and will end in February 2018. A minimum of 500 residents per country are included into the study (Total *N* = 1000 residents). This number has been estimated as a representative sample, as the population of nursing homes is relatively homogenous compared to community dwelling populations. The project is divided into four main study phases: Phase 1: Development and piloting of a common study protocol, Phase 2: Quantitative Data collection, Phase 3: Qualitative data collection, Phase 4: Analysis of data and publication of results.

A common working definition for the term ‘nursing home’ was agreed upon, as cross-country differences in institutionalized elderly care and different ideas on what necessary features constitute a nursing home exist. According to Sanford et al. [32], nursing homes are characterized by the following five parameters: (1) provides 24-h functional support for people who require assistance with activities of daily living (ADL)/instrumental activities of daily living (IADL) and have identified health needs; (2) may or may not be staffed with health care professionals; (3) provides long term care and/or rehabilitation as part of hospital avoidance or facilitate early hospital discharge; (4) does not function as a hospital ward and is not hospital based; (5) may play a role in providing palliative and/or hospice care at end of life.

There are currently 886 nursing homes in Austria and 822 in the Czech Republic. In Austria, there are three categories of nursing homes: (1) Homes under the administration of the federal state. In Upper Austria, these homes are managed by a commissioned organisation called *Sozialhilfeverband* (Social Help Organisation), (2) Homes under the administration of the municipality and (3) private homes of religious organizations or for profit organizations. To be admitted to a nursing home in Austria, a person needs to have a minimum level of care. The Austrian care system has seven levels of care. Each care level is defined by hours of care per month and person. Potential nursing home residents need to be ranked at a minimum level of 3, which is defined as: a person needing at least a care effort of 120 h/month.

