### Sampling procedure

#### Austria

The 137 nursing homes of Upper Austria (from a total of 886 nursing home in Austria) formed the basis for the Austrian randomized selection process (see Fig. 1)﻿. Nine homes had to be excluded from the study, because they were “under renovation”. The remaining Austrian sample of 128 nursing homes includes facilities with 60–120 residents. From the remaining 128 homes, 82 nursing homes are run by the federal state, 21 are under municipal administration and 25 are organized by the church or private organizations. Each nursing home was assigned an identification number (ID). All numbers were written on separate pieces of paper and folded, concealing the ID number. The folded papers where then placed in different bowls representing the three organisational categories. Taking the drop outs into consideration, 16 nursing homes were randomly selected in a stratified fashion from the bowls (50% federal state; 25% municipality, 25% church/private). With this method, 16 nursing homes (8 federal state homes, and 4 municipal homes and 4 privately run homes) were randomly drawn. Of these 16 homes, seven nursing homes (five nursing homes run by the federal state, one home run by municipality and one home run by the church) consented to participate. In total, 644 residents are included in the Austrian sample.

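### The country tests named for resident, staff and relative data ignore clustering within 7 Austrian and 9 or 10 Czech homes, so their p-values are too small, by an amount that depends on the ICC

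*Protocol article*

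**What the plan says.** In the protocol article, the section Statistical analysis plan and statistical considerations first describes a multilevel regression, run separately in each country, for neuropsychiatric symptoms. It then turns to outliers and differences between the countries. The test is chosen "Depending on the level of measurement" from Student's t, Mann-Whitney U and chi-square: "Test will be used – especially for country comparison". A pooled analysis follows, with random effect models in which country is the only random factor named. The home is not mentioned for the country tests or for the pooled models.

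The sampling unit is stated under Study design: "Stratified and randomly drawn nursing homes in Austria and the Czech Republic are surveyed". Under Sampling procedure, Austria has "seven nursing homes (five nursing homes run by the federal state, one home run by municipality and one home run by the church", and "In total, 644 residents are included in the Austrian sample". The Czech sample is 570 residents. The homes for seniors are given as "6 nursing homes (3 municipal, 1 for-profit and 1 non-profit) consented to participate", and the homes with a special regime as "four nursing homes (2 municipal, 1 for-profit and 1 non-profit) consented to participate". Czech homes differ greatly in size: "the smallest home provides services for 8 residents, whereas the biggest home provides care for 260 residents".

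**The concern.** The three named tests assume independent observations. Residents of one home share staff, admission practice, routines and assessor visits, so their values tend to be alike. The plan itself expects homes to differ: it models behavioural symptoms on home size and staffing, and uses a multilevel model to do so. That structure is dropped for the country comparison, where the information comes from about 17 homes rather than 1,214 residents (644 + 570).

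At stake is the reading of country differences. The Discussion expects such differences to show a possible need to change practice in homes in both countries. If the tests ignore the home, ordinary variation among a handful of homes can appear as a significant difference between two national care systems.

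**Working it through.** **Inputs from the article.** Austria: 644 residents in 5 + 1 + 1 = 7 homes, mean 644/7 = 92. Czech Republic: 570 residents in 6 + 4 = 10 homes, mean 57. The listed sub-categories of homes for seniors add to 3 + 1 + 1 = 5, which would give 9 homes. Czech homes serve 8 to 260 residents.

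**Assumptions.** Two-sided alpha 0.05 and ICC from 0.005 to 0.10. The article gives neither, and it states no error rate or design effect that could be reproduced.

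**Formulas.**
- Design effect per country: DE = 1 + (Σn²/N − 1) × ICC. With equal homes, Σn²/N is the home size.
- Design effect of the difference: D = (DE_A/644 + DE_C/570) / (1/644 + 1/570).
- True type I error of the unadjusted test: 2 × [1 − Φ(1.96/√D)].

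**Equal home sizes, 7 × 92 versus 10 × 57, at ICC 0.05.**
- DE_A = 1 + 91 × 0.05 = 5.55.
- DE_C = 1 + 56 × 0.05 = 3.80.
- D = 4.62, √D = 2.15, and the error is 2 × [1 − Φ(0.91)] = 0.36.
- Effective sample sizes: 644/5.55 = 116 and 570/3.80 = 150.

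**Unequal Czech homes (illustrative): 260, 8 and eight of 37.75, at ICC 0.05.**
- Σn²/N = (67,600 + 64 + 11,400.5)/570 = 138.7.
- DE_C = 1 + 137.7 × 0.05 = 7.89.
- D = 6.79, √D = 2.61, and the error is 0.45.

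| ICC | D, equal homes | Type I error, equal | D, unequal Czech homes | Type I error, unequal |
|---|---|---|---|---|
| 0.005 | 1.36 | 9% | 1.58 | 12% |
| 0.01 | 1.72 | 14% | 2.16 | 18% |
| 0.05 | 4.62 | 36% | 6.79 | 45% |
| 0.10 | 8.24 | 50% | 12.58 | 58% |

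**Sensitivity.** With 9 equal Czech homes the error is 14% at ICC 0.01 and 37% at 0.05. With the planned minimum of 500 residents per country, in 7 and 10 homes, it is 12% and 33%.

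**Check by simulation.** There was no true country difference; 4,000 runs were made (2,000 for Mann-Whitney), with equal homes and an assumed 70% prevalence for the chi-square test. Rejection rates for t / Mann-Whitney / chi-square were 0.13/0.13/0.14 at ICC 0.01, 0.36/0.35/0.35 at 0.05 and 0.49/0.49/0.50 at 0.10. At ICC 0 all three were close to 0.05. A t-test on home means kept its level: 0.042 to 0.048 with equal homes and 0.039 to 0.045 with unequal Czech homes, over ICC 0.01 to 0.10.

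**Do the other planned models help?** The multilevel regression is fitted within each country, so it contains no country contrast. The pooled model treats country as random with only two levels and names no home effect. It therefore neither accounts for clustering by home nor gives a usable test of the country difference.

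**The case against.** The best defence is that these tests are a preliminary look at the data. The sentence before them speaks of checking distributions, and models follow. The study is a survey with a special focus on dementia prevalence, its own limitations paragraph calls the work exploratory, and no primary country hypothesis or alpha is stated. This stands in part: the per-country prevalence point estimates and the per-country multilevel regressions do not depend on these tests. It does not rescue the tests, because country difference is their named purpose and no other stated analysis tests it validly.

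Stronger readings that a reader might infer are not supported:
- **That the error rate is several times nominal whatever the outcome.** No ICC is given. At 0.005 the inflation is only about two-fold (9% to 12%).
- **That whole homes were enrolled, or that one home supplies 260/570 = 46% of the Czech sample.** Residents needed signed consent, and those in acute crisis or dying were excluded. The 260 is the number of residents the home cares for, not the number enrolled, so 46% is an upper bound.
- **That every country comparison is affected.** Environmental variables are recorded once per home, and clustering within homes does not inflate ordinary tests on those.

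**Conclusion.** The point holds for person-level variables. As written, the country tests ignore the home, and nothing else in the section corrects this. With equal home sizes and two-sided alpha 0.05, a nominal 5% test has a true error of about 9% at ICC 0.005, 14% at 0.01, 36% at 0.05 and 50% at 0.10. If Czech enrolment followed the stated extremes of home size, the figures would be 12%, 18%, 45% and 58%. The direction is certain for any positive ICC. The size rests on the assumed ICC and on how enrolment is spread over homes, neither of which the article gives. Whether there are 9 or 10 Czech homes hardly matters. The wording should change before any p-value for a country difference is reported.

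**What to change.** Amend the analysis section as follows.

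- **Continuous person-level outcomes** (residents, staff, relatives): test country as a fixed effect in a linear mixed model with a random intercept for home and Satterthwaite or Kenward-Roger degrees of freedom.
- **Binary and ordinal person-level outcomes:** take inference from a home-level analysis, that is, a t-test or permutation test on home means or proportions. The degrees-of-freedom corrections above belong to linear mixed models and should not be assumed to carry over to logistic or ordinal ones.
- **Pooled models:** make country fixed and home random.
- **Unadjusted country summaries:** report them without p-values.
- **Variables recorded once per home:** the ordinary two-sample tests may stay.
- **Number of Czech homes:** reconcile the stated 6 homes for seniors with the 5 listed, since the home is the unit of inference.

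The cost is a rewritten paragraph and additional R code; no new data are needed. Intervals will be wider and fewer country differences will be significant, since a home-level t-test has 7 + 10 − 2 = 15 degrees of freedom (14 with 9 Czech homes). Unweighted home means also give a home of 8 the same weight as one of 260, so the report should say whether it describes the average home or the average resident.

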The strength of this multicentre mixed methods cross-sectional study is the size of the study population across countries, the harmonized study protocol with a broad range of variables and the storage of the data in a common database. By means of this data collection, key questions for future care planning can be addressed such as the prevalence of cognitive impairment and dementia within the nursing home milieu. Other important issues such as the influence of environmental factors on the development of behavioural symptoms – a factor which is extremely burdensome for resident, care team members and relatives alike. Potential country differences between Austria and the Czech Republic may demonstrate the necessity to modify old routines, structures and processes in the nursing homes in both countries and enable a cross-country dialogue. Currently, the scale, form and quality of long-term care provision in different countries is variable, suggesting considerable scope for sharing and learning from different national experiences [22]. Since there is still a significant paucity of knowledge in this area, the results of the qualitative part will serve for hypothesis building and recommendations for future research. Through understanding the unmet needs of residents with dementia, treatment plans and care concepts can be created which form the basis for nonpharmacological interventions [51]. There seems to be no doubt that specific care models for persons with dementia are required [20] and non-pharmacological interventions should be advanced. This study endeavours to enter into the discussions on these important matters providing further epidemiologic basic data. DEMDATA also has the potential to attract other countries to join this initiative for future projects, thus promoting further international co-operations. One of the major strengths of this study is, that the data will be assessed by trained researchers whereas other studies used untrained nursing staff for the assessment of residents and other variables [10]. Even though using untrained nursing home staff makes bigger data samples possible, working with trained researchers heightens the data quality. Since this project envisions to prepare the data for sharing, the quality of the produced data is of the utmost importance.

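### The pooled models treat country, a two-level factor fixed by design, as random and name no nursing-home effect, although homes are the sampled clusters

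*Protocol article*

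**What the plan says.** The section of the protocol article on statistical analysis sets out three steps.

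- Per country: "A multilevel regression analysis will be performed per country to estimate the influence of different environmental and other factors" on neuropsychiatric symptoms. The environmental examples are factors that vary between homes ("e.g. the size of the nursing home, and patient/staff ratio").
- Between countries: a t-test, Mann-Whitney or chi-square test, according to the type of variable, "will be used – especially for country comparison".
- Pooled: for the outcome variables, "random effect models with the respective country as random factor will be conducted". No other random term is named for this step.

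On sampling, the Study design section says: "Stratified and randomly drawn nursing homes in Austria and the Czech Republic are surveyed". In Austria the account reads "Of these 16 homes, seven nursing homes" agreed to take part, and "In total, 644 residents are included in the Austrian sample". In the Czech Republic six homes for seniors and four special-regime homes agreed, with 570 residents. The bracket for the homes for seniors adds to 3 + 1 + 1 = 5, so there are 10 Czech homes as stated or 9 by the bracketed counts.

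The Discussion treats the contrast between the countries as a result in its own right: "Potential country differences between Austria and the Czech Republic may demonstrate the necessity to modify old routines".

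**The concern.** A random effect suits a factor whose levels are a sample from a larger set and are numerous enough to estimate a variance. Nursing homes meet that description here. Country does not: it has two levels, both chosen in advance, and their difference is something the study wants to report. The pooled sentence gives the random role to country and is silent on home.

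Two consequences follow whatever is done about homes. The country variance is estimated from two points, and the country difference does not appear as a coefficient with an interval. A third consequence is conditional. If the sentence is followed literally and no home term is added, residents of the same home are treated as independent within country, and any predictor that varies between homes gets too small a standard error. Associations between features of a home and its residents' symptoms could then be reported too readily, in a study meant to inform care planning.

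**Working it through.** The section gives no figure for the pooled model, so there is none to reproduce. The inputs from the document are 7 Austrian homes with 644 residents (644/7 = 92 per home), 10 Czech homes with 570 residents (57 per home), a Czech home size range of 8 to 260, and two countries. The home ICC is not given and is varied from 0.01 to 0.20 as an assumption.

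**1. Information on the country variance.** With k = 2 levels, df = 1. The 95% interval for a variance, as a multiple of its estimate, is df/χ²(0.975) to df/χ²(0.025):

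- Country random, 1 df: 1/5.024 = 0.20 to 1/0.000982 = 1018 (0.45 to 32 on the SD scale).
- Home random with country fixed, 17 − 2 = 15 df: about 0.55 to 2.40. With 16 homes, 14 df: about 0.54 to 2.49.

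**2. How often the country variance is estimated as zero.** Take residual SD 1 and no home effect. The sampling variance of the country difference is 1/644 + 1/570 = 0.00331. A true country SD of 0.3 adds 2 × 0.09 = 0.18. The estimate is zero when the squared observed difference falls below 0.00331, which has probability P(|Z| < √(0.00331/0.18331)) = P(|Z| < 0.134) = 0.11. Simulation agrees: 11% of estimates are exactly zero, and the central 95% of the estimated SDs run from 0 to 0.68. With a true country variance of 0.05 and home clustering present, simulation gave 11–15% zeros.

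**3. Standard errors if home is omitted.** Design effect = 1 + (Σm²/Σm − 1) × ICC, where m is the number of residents per home. With equal Czech homes, Σm²/Σm = (7 × 92² + 10 × 57²)/1214 = 91,738/1214 = 75.6. At ICC 0.05 this gives 1 + 74.6 × 0.05 = 4.73, and √4.73 = 2.2. The unequal case assumes Czech homes of 8, 260 and eight equal homes sharing the remaining 302 residents.

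**4. Type I error for a home-level predictor with no true effect**, nominal 5%, with country as the only grouping term. Two simulations were run. One had equal Czech homes and adjusted by centring within country (3,000 runs per ICC). The other had Czech homes of 8 to 260 and a fitted random country intercept (2,000 runs per setting).

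| Assumed ICC | Design effect | SE too small by | Type I error, equal homes | Type I error, unequal homes |
|---|---|---|---|---|
| 0.01 | 1.75–2.13 | 1.3–1.5 | 14% | 15–16% |
| 0.02 | 2.49–3.26 | 1.6–1.8 | 21% | not run |
| 0.05 | 4.73–6.65 | 2.2–2.6 | 36% | 39–40% |
| 0.10 | 8.46–12.29 | 2.9–3.5 | 49% | 52–55% |
| 0.20 | 15.91–23.59 | 4.0–4.9 | 64% | not run |

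For a resident-level predictor that does not cluster by home, type I error stayed at 4–5%. For one with its own ICC of 0.10 it was 9% at an outcome ICC of 0.05 and 12% at 0.10.

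**5. Effect of the remedy.** In a small check (20 data sets, ICC 0.05), the mean standard error of a home-level predictor rose from 0.030 with country alone as random to 0.064 with country fixed and home random. The mean ratio was 2.1, in line with step 3.

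**The case against.** The strongest reply is that the sentence does not exclude a home term. It does not call country the only random factor. The per-country model is called multilevel, which within one country most naturally means residents within homes, and the pooled model may be meant to add country above that structure. A journal article also leaves a full list of model terms to a later plan. This stands as far as it goes: a reader might infer that homes are deliberately left out, and the text does not support that. It does not rescue the choice of country as a random factor, which the text states.

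The section also ties environment and staffing explicitly to the per-country regressions, and names no home-level predictor for the pooled models. So the inflated error rates apply only if such predictors enter the pooled models and home does not.

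Three further strong readings fail. The country variance is not inestimable: it can be computed, but on 1 degree of freedom. Standard errors are not far too small throughout: at ICC 0.01 the understatement is moderate, and for resident-level predictors that do not cluster by home there is none. Nor does shrinkage hide the country difference. With about 600 residents per country, country variance 0.05, residual variance 1 and no home effect, the factor is 0.05/(0.05 + 1/600) = 0.97. The country comparison is also planned separately through two-sample tests. Whether those should allow for clustering is another question.

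Finally, 8 and 260 are the numbers of residents those homes serve, not confirmed enrolment. That is why the equal-homes results are shown alongside.

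**Conclusion.** The point holds in limited form. Naming a two-level, design-fixed factor as random is a model choice the article makes, and it fits the design poorly. Its direct cost needs no ICC assumption: a practically uninformative country variance, and no country coefficient with a confidence interval from the pooled model.

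The damage to standard errors is conditional on three things: no home term in the fitted model, a predictor that varies between homes, and a home ICC above zero. Under those conditions type I error is about 14–16% at ICC 0.01, 36–40% at 0.05 and 49–55% at 0.10. The true ICC is unknown. Whether there are 9 or 10 Czech homes does not change the conclusion, though the counts should be reconciled.

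This should be corrected before the pooled analysis is run. It does not touch the descriptive prevalence results, and the article itself presents the associations as exploratory.

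**What to change.** In the pooled models, enter country as a fixed effect and nursing home, nested in country, as a random intercept, and say so in the text. For continuous outcomes use Satterthwaite or Kenward-Roger degrees of freedom, because inference on home-level factors and on country rests on about 15 degrees of freedom rather than on 1,214 residents. Report the country coefficient with its confidence interval. Where the question is whether a factor acts differently in the two countries, add a country-by-factor interaction.

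The change costs one sentence in the statistical section and one line of R code, and needs no new data. The downside is wider confidence intervals for home-level factors (about twice as wide at ICC 0.05) and for the country contrast, so some associations will no longer be distinguishable from chance. With 16 or 17 homes, few home-level predictors can be fitted at once.
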